**Primary outcome**									
Pain intensity (NRS)		x					x	x	
**Secondary outcome**									
Pain intensity (NRS)			x	x	x	x			
Health-related quality of life (SF-36 and SF-6D)		x				x		x	x
**Interventions**									
Active TENS			x	x		x			
Placebo TENS			x	x		x			
Educational Booklet			x						

To evaluate pain intensity, an 11-point NRS will be used, where 0 (zero) represents no pain and 10 (ten) represents the greatest imaginable pain. Participants will be instructed to rank their pain according to the appropriate point of the scale [35].

Health-related quality of life will be evaluated for Short-Form 6 dimensions (SF-6D) [36, 37], a multi-attribute utility instrument translated and validated to Portuguese/Brazil [38]. It measures health on six dimensions: physical functioning, role limitations, social functioning, pain, mental health, and vitality. The SF-6D unique score varies from 0 (worst health state) to 1 (best health state) and represents the strength of an individual’s preference for a given health state.

Conventionally, it has been recommended to use SF-6D together with the 36-Item Short Form Health Survey questionnaire (SF-36) [37]. The SF-36 [39, 40] assesses health-related quality of life in eight domains: physical functioning, role physical, bodily pain, general health, vitality, social functioning, role-emotional, and mental health. The SF-36 scores represent a health status and range from 0 (worst health status) to 100 (best health status) for each domain.

The baseline assessment will be performed face-to-face for all participants. Participants allocated to the TENS groups will respond to pain intensity face-to-face, before and after each treatment session, during three consecutive menstrual cycles. During this period, participants allocated to the educational booklet will be assessed using text messages and/or video calls with WhatsApp®. In the three-month assessment, the participants of all groups will also be asked about their satisfaction with the treatment. The 6- and 12-month assessments will be conducted using WhatsApp®. The timeline for the schedule for enrollment, assessment, and interventions is presented in Table 1.

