### Assessment of clinical outcomes

Participants who agree to participate will be assessed by a blinded assessor who will check for eligibility criteria. Subsequently, the blinded assessor will collect participants’ demographic and anthropometric data and information regarding menstrual pain medication use. Next, all eligible participants will be randomized and allocated into three groups: active TENS (aTENS), placebo TENS (pTENS), and minimum intervention group (booklet). The same blinded assessor will evaluate primary and secondary outcomes.

The primary outcome is pain intensity at baseline and three and six months after randomization. The secondary outcomes are pain intensity (only at 12 months after randomization, for the cost-utility analysis), health-related quality of life at 6 and 12 months after randomization, and pain intensity at each session before and after treatment for three months for the TENS groups. All assessment sessions are described in Table 1.

**Table 1 pone.0250111.t001:** Timeline for the schedule of enrollment, assessments, and interventions.

	Enrollment	Month 1		Month 2		Month 3		Follow-up	
		Baseline	Post	Pre	Post	Pre	Post	Month 6	Month 12
Eligibility criteria	x								
Informed consent	x								
Demographic and anthropometric data	x								

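### At month 3 the primary pain score differs between the TENS and booklet arms in contact mode, and probably in timing, so TENS-versus-booklet contrasts at that visit are confounded

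*Protocol article*

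**What the plan says.** All places are in the Protocol article.

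- **Primary outcome** (Assessment of clinical outcomes): "The primary outcome is pain intensity at baseline and three and six months after randomization". Table 1 marks it under Baseline, Month 3 Post and Month 6.
- **Session scores** (same section): the secondary outcomes include "pain intensity at each session before and after treatment for three months for the TENS groups". The secondary pain row of Table 1 is marked at Month 1 Post, Month 2 Pre and Post, and Month 3 Pre.
- **TENS arms, cycles 1 to 3** (text below Table 1): "Participants allocated to the TENS groups will respond to pain intensity face-to-face, before and after each treatment session, during three consecutive menstrual cycles".
- **Booklet arm, same period** (next sentence but one in sense, same paragraph): "During this period, participants allocated to the educational booklet will be assessed using text messages and/or video calls". The Interventions section says that this arm gets nothing beyond the booklet.
- **Other time points** (same paragraph): baseline is in person for everyone; months 6 and 12 are by WhatsApp for everyone.
- **Assessor** (Assessment of clinical outcomes): "The same blinded assessor will evaluate primary and secondary outcomes".
- **Analysis** (Statistical analysis): a linear mixed model with group, time and their interaction.

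**The concern.** A between-arm comparison at a given visit needs the outcome to be obtained in the same way in each arm. Here the 3-month primary score appears to come from a face-to-face rating after a supervised session in two arms, and from a text or video contact with no stated position in the menstrual cycle in the third. Dysmenorrhea pain is episodic: the Eligibility criteria place it between 48 h before menstruation and 72 h after its first day. When the question is asked, and in what setting, can therefore change the answer.

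Active TENS versus booklet is one of the two comparisons in the hypothesis stated in the Abstract, so a primary contrast is at stake. Within the TENS arms, the change from month 3 to month 6 bears on durability, and it would also contain a switch of mode and timing. In addition, the assessor described as blinded also collects the session scores. Meeting some participants at sessions and contacting others only remotely tends to reveal who is in the booklet arm.

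**Working it through.** The point rests on the schedule, not on a figure in the plan, so there is no stated number to reproduce.

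**Step 1: what Month 3 Post is.** A before-and-after series over three cycles needs six scores. The secondary row of Table 1 supplies four: Month 1 Post, Month 2 Pre, Month 2 Post and Month 3 Pre. The two that complete the series, Month 1 Baseline and Month 3 Post, appear only in the primary row. TENS is marked under Month 3 Pre. The Month 3 Post primary score is thus most naturally the score after the session, and no other 3-month pain score is described.

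**Step 2: the primary score by arm.**

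| Time point | Active and placebo TENS | Booklet |
|---|---|---|
| Baseline | in person | in person |
| Month 3 | in person, after a session (natural reading) | text and/or video, no session, no anchor stated |
| Month 6 | WhatsApp | WhatsApp |

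**Step 3: what the model estimates.** Let τ be the true month-3 difference on a common measurement, and let m(T) and m(B) be the shifts due to mode and timing in the TENS and booklet arms.

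- Active TENS minus booklet at month 3 estimates τ + m(T) − m(B). The shift is fixed by arm, so neither the group-by-time term nor a covariate can remove it.
- Placebo TENS minus booklet contains the same m(T) − m(B).
- Active minus placebo TENS: both arms are measured alike, so an additive shift common to them cancels.
- Month 6: all arms share one mode and no session is involved, so no such term arises between arms.
- Month 3 to month 6 within a TENS arm: the change includes the move from in-person post-session to remote scoring.

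**Step 4: illustration of size.** The article gives neither an SD for the pain score nor a value for the shift; both are assumed here. Completers per arm: 58 × 0.85 = 49.3, taken as 49. Set τ = 0 and let the shift be δ. The chance of a significant result at two-sided 5% is approximately

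Φ(δ / (SD × √(2/49)) − 1.96),

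where the opposite tail adds less than 0.2 percentage points.

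| SD | SE = SD × √(2/49) | δ = 0.5: ratio, chance | δ = 1.0: ratio, chance |
|---|---|---|---|
| 1.5 | 0.303 | 1.650, 38% | 3.300, 91% |
| 2.0 | 0.404 | 1.237, 24% | 2.475, 70% |
| 2.5 | 0.505 | 0.990, 17% | 1.980, 51% |

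The nominal rate is 5%.

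**The case against.** **The timing is inferred.** The text lists the 3-month primary score separately from the session scores, and it mentions a 3-month assessment of all groups (for satisfaction) without giving its mode. Table 1's columns are not a strict before/after code either: TENS is marked under Post in Month 1 but under Pre in Months 2 and 3, and the booklet is marked under Post. Post at Month 3 could mean end of treatment. This stands as a limit. A reader might infer that the TENS score is taken straight after stimulation, but no interval is stated. The difference in contact mode during the three cycles is stated outright.

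**The reach is narrow.** Active versus placebo TENS is measured alike, month 6 is alike in all arms, and the Strengths and weaknesses section already concedes that booklet participants are unblinded. All true. That concession does not mention mode or timing, however, and leaves the month-3 booklet contrasts exposed.

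**Part of the difference is treatment.** Relief after a session is partly what TENS does, so not all of a timing difference is bias. This also stands. It argues for keeping the post-session score as an acute outcome, not for comparing it with a score in an arm that has no session.

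**Further inferences the article does not support.**
- That the biased score feeds the cost-effectiveness ratio: the Economic assessment and Statistical analysis sections name the pain scale but not the time point, so this is possible and not established.
- That the instrument changes between months 3 and 6: it is the same 11-point scale, and only mode and probably timing change.
- That a 1-point shift would equal the whole planned effect: this needs an assumed SD of 2 and a reading of f = 0.20 as a between-groups effect, whereas the Sample size calculation names only repeated-measures analysis of variance.

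**Conclusion.** The concern holds in this form. At a primary time point, contact mode is confounded with arm for active or placebo TENS versus booklet; on the natural reading of Table 1, timing is confounded too. The 3- to 6-month change in the TENS arms mixes durability with the change in collection, and remote contact tends to disclose booklet membership to the assessor. Active versus placebo TENS and the month-6 between-arm contrasts are sound on this point.

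The size and direction of the bias are unknown. The 17% to 38% for a 0.5-point shift shows only that a modest artefact could matter at this sample size. It rests on the assumed SDs, 49 completers per arm, no true effect, and a simple two-group comparison in place of the mixed model. The confounding cannot be removed by analysis once the scores have been collected.

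**What to change.** - Define one primary pain score for all three arms at baseline, month 3 and month 6: the same question and the same recall window anchored to menstruation, not tied to a session. Worst pain over a stated part of the menstrual period is one option; the choice of window is the investigators'.
- Use the same mode in all arms at each time point. At month 3 the item can be added to the WhatsApp contact already used for the cost questionnaire. Baseline is already in person for all arms and needs only the same question and window.
- Keep the face-to-face scores before and after sessions as a secondary, acute-effect outcome for active versus placebo TENS.
- In Table 1, move the 3-month primary mark out of the Post column into a 3-month assessment column common to all arms.

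The cost is one added item at baseline and one at month 3. The downside is that the primary score becomes recalled rather than momentary pain.

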### Economic assessment

Economic assessment will be done from a healthcare and societal perspective. Incremental cost per quality-adjusted life-years (QALYs) of the interventions will be used for cost-effectiveness and cost-utility analysis, considering both healthcare and societal perspectives, measuring direct and indirect costs. The Numerical Rating Scale will be used for cost-effectiveness analysis, and the SF-6D questionnaire will be used for cost-utility analysis. Cost data will be collected by a cost questionnaire that will be sent to the participant via WhatsApp® at 3, 6, and 12 months after baseline. All costs related to menstrual pain will be considered, either direct (costs of the participant to health systems, public and private, and out-of-pocket expenses) and indirect (unpaid productivity loss), which include intervention, healthcare, informal care, and unpaid productivity costs. Intervention costs will be estimated based on the physical therapy board fee schedule (according to the Federal Physical Therapy and Occupational Therapy Council, USD 11.32 per TENS application– 2020 fee which is equivalent to R$ 64.63 rate converted to US dollars using the 04/02/2021 conversation rate [41]). Healthcare costs, including primary and secondary healthcare costs, will be priced using Brazilian standard costs. Both prescribed and over-the-counter medication use will be priced using the prices of the Brazilian pharmaceutical websites and medical services fee schedule.

A Portuguese/Brazil validated version [42] of the Stanford Presenteeism Scale [43] will be used to measure presenteeism from paid work, and the estimated price of productivity losses per sickness absence day for women, according to the average wage in the state of São Paulo per hour.

### Randomization and concealed allocation

Prior to the baseline assessment, participants will be randomized into three groups: aTENS, pTENS, and booklet. Randomization will be generated by a computer program, “Randomization Main,” and performed by a participating researcher not involved with the participants’ recruitment or evaluation. The age range for participants is relatively broad, but both the eligibility criteria and the randomization process help to ensure that groups will be equivalent at the beginning of the experiment, turning them comparable at the end of the experiment [44]. Concealed allocation will be achieved using sequentially numbered, sealed, and opaque envelopes. The envelopes will be stored in a safe cabinet that only the allocation investigator will have access to; the envelopes will not be opened until immediately prior to the first intervention session [45]. The allocation ratio will be 1:1:1.

### Interventions

For the TENS group, two Neurodyn II (IBRAMED ®, Brazil) devices will be used. Before starting the trial, one researcher not involved in the study will assign a number (1 or 2) to each of the two TENS devices: one to be the active TENS, while the other will be programed by IBRAMED ® to be used as a placebo. To achieve and ensure blinding in the pTENS group, the participants will be connected to the TENS unit in the exact same way as participants of the aTENS. The active indicator of the unit emits light and sound just as the active device but will deliver electrical stimulation in the placebo mode, described below. Participants and physical therapists will be blinded throughout the treatment.

To report the TENS parameters, the recommendations of Barbosa et al. [46] were followed. The protocol was based on Machado et al. [47]: a balanced asymmetric biphasic pulsed will be used in transcutaneous application mode. Two silicone rubber and carbonate electrodes (5X3 cm, Quark®, Brazil) will be coupled with a conductive gel and fixed on both sides of the lower abdomen at the T10-T11 level with micropore tape. The positioning of the electrodes can be observed in Fig 1. The active TENS parameters will be a frequency of 100 Hz, 200 μs pulse duration, and maximal but comfortable current amplitude (sensory level). The current amplitude will be increased until the participant reports feeling the current as a strong tingling sensation [48]. The amplitude will be registered during the entire treatment session. For the placebo TENS, the device will release current with the same parameters (F = 100 Hz, pulse duration of 200 μs) but for only 30 s, and then the current will be ramped off over a 15-s time frame. All participants, including those allocated to the pTENS, will be asked about their sensations during stimulation every 5 min. If a participant in the aTENS perceives a lower sensation, the current amplitude will increase until the sensation is felt again. The current amplitude will not be increased until the motor level, which means that if the motor level is reached, the current amplitude will not be further increased. The pTENS group will also be queried on its intensity every 5 min, and if they ask about the lack of sensation, they will receive an explanation that this is expected on the basis of the sensory habituation that occurs in most people with TENS application [49].

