### Strengths and weaknesses of the study

The strengths of the present study are that this is the first prospective study that aimed to assess the cost-effectiveness of TENS for PD pain. This is a randomized controlled clinical trial in which researchers, participants, and physical therapists are blinded to participants’ allocation and to the aim of the present study. The sample size was appropriately calculated to provide enough power to detect differences in the primary outcome. The statistical plan analysis includes the intention-to-treat analysis and intends to assess all women who discontinue intervention. One limitation of the present study is that even though participants allocated to the TENS groups (both active and placebo) will be blinded to their allocation, it is not possible to blind participants in the Booklet group.

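### Therapist blinding is claimed without qualification, but the TENS session procedure as written does not secure it

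*Protocol article*

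**What the plan says.** The Interventions section of the protocol article makes the claim without a qualifier: "Participants and physical therapists will be blinded throughout the treatment". The section on strengths and weaknesses repeats it: "This is a randomized controlled clinical trial in which researchers, participants, and physical therapists are blinded". The only blinding limitation admitted there is that "it is not possible to blind participants in the Booklet group".

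Several masking measures are described under Interventions. A researcher outside the study numbers the two devices before the trial starts, the manufacturer programs one as the placebo, and electrodes are connected identically. For the placebo unit, "The active indicator of the unit emits light and sound just as the active device". The question put to participants is also common to both arms: "All participants, including those allocated to the pTENS, will be asked about their sensations during stimulation every 5 min".

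The response to the answer is not worded in common. For active TENS: "If a participant in the aTENS perceives a lower sensation, the current amplitude will increase until the sensation is felt again". For placebo TENS: "if they ask about the lack of sensation, they will receive an explanation that this is expected on the basis of the sensory habituation". No amplitude increase is mentioned for the placebo arm.

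**The concern.** Each of the two response sentences names an arm. A therapist who follows them as worded must know which arm the participant is in, and the claim of blinding denies the therapist that knowledge. The masking measures cover the device and the question; none covers the response.

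Active versus placebo TENS is the only contrast in which participants are meant to be blinded, and pain is self-rated. A therapist who knows or guesses the arm may change expectation, encouragement or attention just before a post-session rating. Even if no bias follows, readers would credit the trial with a safeguard that its stated procedure does not deliver.

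**Working it through.** This is a check of internal consistency. The protocol article gives no figure to reproduce.

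**1. The common and arm-specific steps side by side (Interventions)**

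| Step | Active TENS | Placebo TENS |
|---|---|---|
| Connection, light, sound | same | same |
| Query about sensation every 5 min | yes | yes |
| Trigger for a response | participant perceives less sensation | participant asks about missing sensation |
| Response | raise amplitude, not beyond motor level | explain habituation; no increase stated |

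The first two rows are the same for both arms and the last two are not. No sentence gives a rule keyed to the device number or to the participant's report alone.

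**2. Who could apply an arm-specific rule?** No unblinded operator is named for the sessions. On envelope access, the randomization section says: "The envelopes will be stored in a safe cabinet that only the allocation investigator will have access to". That role is given no session task. This silence does not show that therapists are told the arm. It does mean that the text offers no one else to apply the rule.

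**3. When does the placebo current stop?** Inputs from Interventions: 30 s of current, then a 15 s ramp-down.

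- Placebo current ends at 30 + 15 = 45 s.
- The first scheduled query is at 5 min = 300 s, which is 300 − 45 = 255 s later.
- The abstract gives 30 min for active stimulation. Assuming placebo sessions last as long, there are 5 queries (5 to 25 min), or 6 if one is made at 30 min.

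So at every scheduled query the placebo participant has no current. How often this leads to a report or question is not stated, but the protocol anticipates it by scripting a reply.

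**4. Can an inference carry over?** There are two devices, one per arm, each with a number assigned before the trial, and no re-coding is described. The planned sample is 174 / 3 = 58 per group. A therapist who once infers which number is the placebo could apply that to every later participant on either device, in a planned 58 per device.

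**5. Which ratings are exposed?** Table 1 marks NRS pain as follows:

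- Primary row: baseline, month 3 post, month 6.
- Secondary row: month 1 post, month 2 pre, month 2 post, month 3 pre.

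The post-session ratings are months 1, 2 and 3 post, so 3 in all. Of the 2 post-baseline primary ratings, 1 (month 3 post) follows a session and 1 (month 6) does not. This counts where an effect could act. It does not measure harm.

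**The case against.** The best counter-argument is that the two sentences can both be followed by a blinded therapist. Their triggers differ: one is a perceived drop in sensation, the other a question from the participant. A therapist who raises the control whenever sensation falls, and explains habituation whenever asked, satisfies both without knowing the arm. The arm labels may simply describe what happens in each group, since only the active unit has a current left to raise. A full session manual may contain such a script, and an article need not print it.

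Part of this stands. It rules out the stronger reading that a reader might infer, namely that therapists are told the allocation or that blinding must fail. The documents do not say what therapists are told, and handling both arms alike is possible.

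It does not rescue the unqualified claim. The point does not rest on a missing script: the article prints an arm-specific procedure next to the statement that therapists are blinded throughout. Even with equal handling, raising the control should restore sensation on one numbered device and, if the placebo output stays at zero, not on the other. The same fact counts against a common script that branches on whether sensation returns, because the branch would itself point to the placebo device.

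It is also fair to say that the consequence is limited. Each participant sees only her own handling, a blinded assessor evaluates the outcomes, and the month 6 rating is taken by WhatsApp and not after a session.

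**Conclusion.** The concern holds in a limited form. The procedure as written does not secure therapist blinding, for two reasons: the response to fading sensation is set by arm, and the placebo current stops at about 45 s on one of only two numbered devices. The unqualified claim in the Interventions section and in the strengths section is therefore not supported. It should be corrected, at modest priority.

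No bias in NRS points can be derived from the document, and any bias is probably limited for the reasons given above. A reader might go further and conclude that the active versus placebo comparison is invalid or that TENS participants are unblinded. The text supports neither conclusion.

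The verdict assumes that the therapist who runs the session also responds to the participant's report, and that device numbers stay fixed during the trial. The document states nothing to the contrary on either point.

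**What to change.** 1. Replace the two arm-worded sentences under Interventions with one response for either device number, triggered only by the participant's report. Suggested text: 'With either device, when a participant reports reduced or absent sensation, the therapist makes the same set adjustment of the amplitude control, staying below motor level, and at the same time explains that habituation is expected.' There should be no further step that depends on whether sensation returns.
2. Before adopting this, confirm with the manufacturer that the placebo unit stays at zero output when its control is turned.
3. In the Interventions and strengths sections, state that therapist blinding is attempted but may be compromised, because therapists can infer the device from participants' reports. Rest the blinding claim on TENS participants and the assessor.

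The cost is one merged instruction, a qualifying phrase in two places and one check of the device. Sample size and visits do not change. There are two downsides. Active titration becomes a set step, repeatable at the next 5-minute query, instead of an increase continued until sensation returns. A placebo participant may also notice that the adjustment has no effect, which could weaken participant blinding, the more important protection for a self-rated outcome. If either is judged unacceptable, leave the handling as it is and withdraw the therapist-blinding claim.
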